### Statistical analysis

Using the “Random” function of the MS-Excel XP® program, a binary series of random numbers will be generated, according to the procedure described by Friedman [34]. This procedure creates the sequence by means of balanced block sampling to ensure a similar number of patients in each group. The series of numbers will be in the possession of the PICU’s head researcher. Depending on that number, each patient will be assigned to one group or the other. If a patient is randomized but does not complete the treatment, their data will not be analysed, and their random number will not be reused.

The categorical variables will be compared using the Chi-square test. The quantitative analysis will be compared using Student’s t-test or the Mann-Whitney U test, depending on whether the sample follows a normal distribution or not. A multivariate logistic regression analysis will be performed on those variables with statistical significance or a clear tendency in the univariate analysis to detect which factors represent a protective factor or not, in terms of quality. The analysis of the interobserver agreement will be performed using Cronbach’s alpha. A *p* < 0.05 will be considered significant. The statistical program SPPS® 20.0 will be used.

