### Inclusion and exclusion criteria

Inclusion: Children under 18 years old with suspected community pneumonia who require admission to the PICU or patients with suspected nosocomial pneumonia during their PICU stay.

Exclusion: Patients with underlying pathologies such as cystic fibrosis or who are immunocompromised. Patients who develop nosocomial pneumonia after being included in the study due to community pneumonia. Patients who have a CXR taken before being admitted to the PICU.

Withdrawal and abandonment criteria: Violation of study protocol, withdrawal of parental consent, death.

Patients withdrawing or with loss of protocol adherence will be excluded from the study.

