### Methodology

The first thing to do will be to obtain consent from the parent(s) or legal guardian(s).

Patients who meet the inclusion criteria and sign the inform consent were randomly assigned to two groups using the “random” function in MS-Excel XP® program. A binary series of random numbers were generated according to the procedure described by Friedman. To procure a similar number of patients in both groups, the procedure created the sequence through a balanced block sampling. The series of numbers were held by the principal investigator and depending on the number of the patient tit was be assigned to on or another group. A total of 8 physicians enrolled participants, and the principal investigator assigned participants to interventions, depending on the randomized list. (Fig. 1)
Experimental Group 1: The paediatrician-researcher (PR) performs the LUS at admission/suspicion as the first lung image test. If the paediatrician assistant (PA) requires a CXR, it can be performed, but the PR will not see the CXR. Patients will be subdivided into 3 groups:
If PCT is < 1 ng/mL and LUS is not suggestive of bacterial pneumonia (normal or viral), the patient will not receive an antibiotic.If LUS is suggestive of bacterial pneumonia, regardless of PCT value, an antibiotic will be recommended.If LUS is not suggestive of bacterial pneumonia, but PCT values are > 1 ng/mL, an antibiotic will be recommended to cover other infectious etiologies.Control Group 2: CXR will be performed as a first lung image test. Criteria to start an antibiotic will depend on the current unit protocol.
If PCT is < 1 ng/mL and CXR is not suggestive of bacterial pneumonia (normal or viral), the patient will not receive an antibiotic.If CXR is suggestive of bacterial pneumonia, regardless of PCT value, an antibiotic will be recommended.If CXR is not suggestive of bacterial pneumonia, but PCT value is > 1 ng/mL, an antibiotic will be recommended to cover other infectious etiologies.

Radiological and ultrasound patterns will be classified as: pneumonia (viral or bacterial), atelectasis, or parapneumonic pleural effusion (Table 2).

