### Outcomes

The antibiotics protocol guided by LUS and PCT will be considered an improvement in the quality of care if a reduction in the prescription of antibiotics is observed, and also if there is a reduction in the number of days on antibiotics. Another primary outcome will be the increase in the sensitivity and specificity when diagnosing bacterial pneumonia using LUS. Secondary outcomes will be the reduction of the irradiation dose using the new protocol (with a reduction in economic costs as well), and a high LUS interobserver agreement.

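### Randomised children are dropped for non-adherence or non-completion, and giving an antibiotic against the no-antibiotic rule is both a protocol departure and a primary outcome event

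*Protocol article*

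**What the plan says.** Three parts of the protocol article bear on who is analysed and for what.

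- **Exclusions.** The Statistical analysis section states: "If a patient is randomized but does not complete the treatment, their data will not be analysed". The Inclusion and exclusion criteria add: "Patients withdrawing or with loss of protocol adherence will be excluded from the study". The same section lists: "Withdrawal and abandonment criteria: Violation of study protocol, withdrawal of parental consent, death".
- **The rule under test.** In Methodology, when PCT is below 1 ng/mL, the experimental arm has: "LUS is not suggestive of bacterial pneumonia (normal or viral), the patient will not receive an antibiotic". The control arm has the same directive: "CXR is not suggestive of bacterial pneumonia (normal or viral), the patient will not receive an antibiotic". The other two branches in each arm are worded more softly, for example: "If LUS is suggestive of bacterial pneumonia, regardless of PCT value, an antibiotic will be recommended".
- **The outcomes.** Under Outcomes, the new protocol counts as an improvement "if a reduction in the prescription of antibiotics is observed, and also if there is a reduction in the number of days on antibiotics". These are primary, alongside diagnostic accuracy.

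The article nowhere mentions an analysis of all randomised children.

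**The concern.** Excluding randomised patients for what happens after randomisation always puts the comparison at risk. Here the risk is sharper, because part of the protocol is itself a decision on antibiotics. In the low-PCT, image-negative branch, a child who is given an antibiotic departs from the protocol and is also a primary outcome event. If that child is dropped for the departure, one prescription leaves the numerator because it was a prescription.

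The same rule applies to both arms, but its effect need not be equal. The experimental arm follows a new LUS-based rule, and the assistant paediatrician may still request a CXR there; the control arm follows the current unit protocol. The share of children in the no-antibiotic branch, and how often that directive is overridden, may therefore differ by arm. Listing death as a withdrawal criterion adds selection on severity, which bears on antibiotic days. At stake is whether the antibiotic comparison still compares the groups that were randomised.

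**Working it through.** **The plan's own figure.** The only computed figure is the sample size, 63 per arm for community pneumonia and 28 per arm for nosocomial pneumonia. The article gives no proportions behind it, so it can be neither reproduced nor refuted. It is used below only to turn percentages into children.

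**Inputs.** Let a be the share of an arm directed to no antibiotic (negative image, PCT below 1), and o the share of those children who are given one anyway. The documents give neither, so all values below are assumptions. For simplicity, every child in the two recommended branches is taken as treated, and overrides are the only departures.

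**Formulas, per arm.**

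- All randomised: 1 − a + a·o
- Overrides dropped: (1 − a) / (1 − a·o)
- Children dropped: 63·a·o
- Downward shift (first line minus second): [a·o / (1 − a·o)] · a(1 − o)

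The shift is never negative, so any override in this branch lowers that arm's analysed rate (unless every child in the branch is overridden). The between-arm difference is unaffected only if the two shifts are equal.

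**Row A worked through.** LUS: 1 − 0.40 + 0.40 × 0.25 = 0.700; after exclusion 0.60 / 0.90 = 0.667. CXR: 1 − 0.30 + 0 = 0.700, unchanged by exclusion.

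| Row | a, LUS v CXR | o, LUS v CXR | All randomised | Overrides dropped | Difference (LUS − CXR), points | Children dropped |
|---|---|---|---|---|---|---|
| A | 40% v 30% | 25% v 0% | 70.0% v 70.0% | 66.7% v 70.0% | 0.0 → −3.3 | 6.3 v 0 |
| B | 40% v 30% | 40% v 15% | 76.0% v 74.5% | 71.4% v 73.3% | +1.5 → −1.9 | 10.1 v 2.8 |
| C | 45% v 30% | 30% v 10% | 68.5% v 73.0% | 63.6% v 72.2% | −4.5 → −8.6 | 8.5 v 1.9 |
| D | 40% v 30% | 15% v 40% | 66.0% v 82.0% | 63.8% v 79.5% | −16.0 → −15.7 | 3.8 v 7.6 |
| E | 40% v 40% | 20% v 20% | 68.0% v 68.0% | 65.2% v 65.2% | 0.0 → 0.0 | 5.0 v 5.0 |
| F | 50% v 30% | 40% v 0% | 70.0% v 70.0% | 62.5% v 70.0% | 0.0 → −7.5 | 12.6 v 0 |

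Rows A and F create a difference where there is none, row B reverses the sign, and row C enlarges a benefit. Row D, with more overrides in the CXR arm, slightly shrinks a benefit. Row E leaves the difference alone but lowers both rates. Swapping the arm labels in row A would make LUS look worse by 3.3 points.

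**Effect on the test.** In a simulation of 100,000 trials with 63 per arm and a two-sided chi-square test at 5%, rejection under equal true prescribing went from 5.0% to 7.0% in row A, from 5.2% to 13.8% in row F, and from 5.1% to 5.2% in row E.

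**The case against.** The strongest objection is that the article defines neither adherence nor completion of treatment, so the link to the outcome is not as tight as it first looks. That stands, and it rules out several stronger readings.

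- **That only prescribed children leave the no-antibiotic branch.** The protocol also fixes which image comes first, keeps the CXR from the researcher in the experimental arm, and requires daily recorded LUS. A child could be excluded for failing any of these, or through withdrawn consent or death, without receiving an antibiotic. The overlap is partial.
- **That analysed prescribing becomes 0% in one branch and 100% in the others.** This would need an unfollowed recommendation to count as a violation. The article only recommends an antibiotic in those branches, so declining one may not be non-adherence.
- **That shortened courses drop out of the days outcome while untreated children never do.** The sentence on completion sits in a paragraph about randomisation and may refer to the allocated study procedure. Determining duration is an objective, so a course shortened under the algorithm may count as completed.
- **That the trial is open and so overrides must be commoner after a negative LUS.** The article calls the trial blinded. It gives no override rate and no direction.
- **That the exclusions must favour LUS.** Rows D and E show they need not, and the shift in row A is modest.

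What the objection does not remove is that both exclusions are written as rules. They are not details left to an analysis plan; a plan that analysed everyone would contradict them. A child given an antibiotic against a flat no-antibiotic directive falls naturally within violation of the protocol.

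**Conclusion.** The concern holds in this form: the article excludes randomised children on post-randomisation events that can coincide with a primary outcome. The overlap is firmest in the low-PCT, image-negative branch of each arm and uncertain in the recommended branches and for incomplete courses. Where overrides in that branch are excluded, the arm's prescribing rate is biased downwards, and the comparison is in general biased when branch shares or override rates differ by arm.

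The document does not allow direction or size to be derived. In the rows shown, the difference moves by between 0 and 7.5 points, wholly on assumed shares and override rates and on the reading that an override is a loss of adherence. Because a plausible case can create or reverse the antibiotic result, this must be corrected before the antibiotic outcomes are analysed.

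**What to change.** Delete the non-completion exclusion from Statistical analysis and the adherence exclusion from Inclusion and exclusion criteria. Replace them with a statement that every randomised child is analysed in the allocated arm for prescription, antibiotic days, irradiation and cost, including children whose no-antibiotic directive was overridden, who did not complete treatment, or who died. Remove data only where consent to their use is withdrawn. State how antibiotic days are counted for children who die. Report overrides and other departures by arm with reasons, and define adherence and completion so that the adherent set can be kept as a labelled sensitivity analysis. None of this alters a clinical rule.

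The cost is a few sentences of text and the retrieval of routine in-house records for non-adherent children. The article dates recruitment and follow-up September 2017 to December 2019, so retrieval may be retrospective; that the records are available is an assumption. The resulting estimate may be less favourable to the algorithm, though the document does not show that it will be.

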### Sample size

Sample size calculations will be performed using the statistical program Ene 2.0®. The main variable will be the existence of differences between CXR and LUS in patients with community pneumonia and nosocomial pneumonia. H1 will be considered as the existence of differences between LUS and CXR. An 80% power will be required to detect differences in the contrast of the null hypothesis H0: p1 = p2, using a bilateral X^2^ test for two independent samples. If we consider a significance level of 5%, it will be necessary to include 63 units in the control group and 63 units in the experimental group. A total of 126 patients will be included for community pneumonia. Twenty-eight patients per group will be included for nosocomial pneumonia; therefore, there will be 56 patients in total for this kind of pneumonia. After 12 months of recruitment, a preliminary analysis will be carried out to guarantee the safety of the patients. Respiratory infection represents around 30–70% of the PICU admissions, depending on the season. There will be an estimated 200–300 recruitable patients per year, so it is expected that the calculated sample size will be attainable.

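### The antibiotic outcomes are compared between arms with valid but unadjusted tests, although entry procalcitonin strongly influences prescribing by the protocol's own rule; stratifying by it would gain precision at almost no cost

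*Protocol article*

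**What the plan says.** All references are to the protocol article.

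- **Outcomes** makes fewer antibiotic prescriptions and fewer days on antibiotics primary outcomes.
- **Statistical analysis** states "The categorical variables will be compared using the Chi-square test" and "The quantitative analysis will be compared using Student’s t-test or the Mann-Whitney U test". It names no stratification or covariate for the arm comparison. Its only multivariable analysis is a logistic regression whose variables are chosen by their univariate results, to look for protective factors.
- **Sample size** rests on the same kind of test, "using a bilateral X^2^ test for two independent samples", with "63 units in the control group and 63 units in the experimental group" for community pneumonia and 28 per group for nosocomial pneumonia.
- **Methodology** gives the rule for the experimental arm: "If LUS is not suggestive of bacterial pneumonia, but PCT values are > 1 ng/mL, an antibiotic will be recommended to cover other infectious etiologies". The control arm has the same rule with chest X-ray in place of ultrasound. In both arms, a child below 1 ng/mL has the decision set by the image.
- Randomisation is in balanced blocks, and no PCT stratum is mentioned.

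**The concern.** If the algorithm is followed, the first image can change prescribing only in children who are not above 1 ng/mL. Above the cut-off both arms receive the same recommendation. Whether a child is above the cut-off is thus a baseline fact, tied to the outcome by protocol rule, that allocation to an image cannot alter. A crude comparison treats this known variation as noise. Two things follow.

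1. The test has less power than the same data could give.
2. If one arm happens to contain more high-PCT children, the observed antibiotic difference moves with it. In the single trial that is run, part of that shift could be read as an effect of ultrasound.

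**Working it through.** **Inputs from the article.** Two-sided alpha 5%, 80% power, 63 per group (community), 28 per group (nosocomial), unadjusted chi-square. No proportions are given; the alternative is only "H1 will be considered as the existence of differences between LUS and CXR".

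**The plan's own figure.** Without proportions, 63 and 28 cannot be reproduced. Inverted with the usual pooled-variance formula, 63 per group detects about 24, 24, 23 and 20 points at control rates of 50%, 70%, 80% and 90%. At the same control rates, 28 per group detects about 32 to 37 points.

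**Assumptions.** Control prescribing 80%, ultrasound arm 57%; share f above 1 ng/mL; prescribing rate h above the cut-off (adherence), equal in both arms.

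**Crude power at 63 per arm.**
- Pooled rate = (0.80 + 0.57)/2 = 0.685.
- SE under the null = √(2 × 0.685 × 0.315/63) = 0.0828.
- SE under the alternative = √((0.80 × 0.20 + 0.57 × 0.43)/63) = 0.0802.
- z = (0.23 − 1.96 × 0.0828)/0.0802 = 0.84, so power is about 80%.

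**Stratified power, worked for f = 0.4 and h = 1.**
- Implied rates at or below the cut-off: control (0.80 − 0.40)/0.60 = 0.667; ultrasound (0.57 − 0.40)/0.60 = 0.283.
- All information sits in 63 × 0.6 = 37.8 children per arm, with a difference of 0.383 and a pooled rate of 0.475.
- SE under the null = √(2 × 0.475 × 0.525/37.8) = 0.115; under the alternative √((0.667 × 0.333 + 0.283 × 0.717)/37.8) = 0.106.
- z = (0.383 − 1.96 × 0.115)/0.106 ≈ 1.49, so power is about 93%.

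**Simulation** of the crude chi-square against the two-stratum Cochran-Mantel-Haenszel test (63 per arm, 80% versus 57%; crude power 80 to 81% throughout). Stratified power:

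| Adherence h above cut-off | f = 20% | f = 30% | f = 40% | f = 50% |
|---|---|---|---|---|
| 100% | 85% | 88% | 93% | 98% |
| 95% | 84% | 86% | 89% | 93% |
| 90% | 83% | 84% | 86% | 89% |
| 80% | 81% | 82% | 82% | 83% |

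With control prescribing of 90% and 90% adherence, the gain is only about 1 to 2 points. With no arm effect, both tests reject in about 5% of trials.

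**Chance imbalance.** The SE of the between-arm difference in the high-PCT share is √(2f(1 − f)/n). At f = 0.4 this is √(2 × 0.4 × 0.6/63) = 0.087 and √(2 × 0.4 × 0.6/28) = 0.131. In the worked case, one such SE at 63 per arm moves the crude prescribing difference by about 0.087 × (1 − (0.667 + 0.283)/2) = 0.046, or 4.6 points.

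**Days on antibiotics.** No gain is computed. The PCT rule governs starting treatment, no section ties duration to PCT, and the article gives no correlation to work from.

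**The case against.** The strongest reply is that nothing here is wrong. Randomisation makes the crude tests valid. Chance imbalance is ordinary sampling error that the p-value already covers, and covariate choices often wait for an analysis plan. The first two parts stand. A reader might infer bias or an inflated false-positive rate; the documents do not support that, and the simulation shows about 5% for both tests. The third part stands only in part, because the article does name the tests.

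Further limits also stand:

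- A reader might infer that the rule fixes prescribing above 1 ng/mL. The article only recommends an antibiotic there, and adds that control-arm criteria follow the unit's current protocol. The gain shrinks quickly as adherence falls.
- The 80% power and 63 per group are not tied to antibiotic prescribing, so using them as the starting point is an assumption.
- The larger gains imply large effects at or below the cut-off: prescribing falling from 67% to 28% at a 40% share, and from 60% to 14% at a 50% share.
- An entry PCT for every child is implied by the classification, but no sampling time is stated.
- A reader might also object that pneumonia type is ignored. The two cohorts are sized separately and nothing says that they are pooled, so this matters only if they are.

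The logistic regression might happen to include arm and PCT. Its variables are chosen from the data, however, so it is no prespecified adjusted arm comparison. It would also approach separation if nearly all high-PCT children are treated.

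**Conclusion.** The point holds as one of efficiency. The stated arm comparison leaves unused a baseline value that the algorithm itself requires and that the protocol links to the outcome. For prescription, the gain runs from about 1 point of power at 80% adherence to about 17 points with full adherence and half of children above the cut-off. This assumes 80% crude power at 63 per arm and 80% control prescribing. At higher control prescribing with imperfect adherence, the gain can be negligible. The benefit for days on antibiotics is plausible through the treated-versus-untreated split but is not quantified. This is a free improvement: the planned tests would not mislead on average, and a result from them would not be invalid.

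**What to change.** In Statistical analysis, replace the generic sentences, for the two antibiotic outcomes only, with the following:

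- **Prescription:** Cochran-Mantel-Haenszel test and Mantel-Haenszel risk difference with 95% CI, stratified by entry PCT (up to 1 versus above 1 ng/mL).
- **Days on antibiotics:** van Elteren test (a stratified Mann-Whitney) with the same strata.
- **Pneumonia type:** add it as a stratification factor only if the community and nosocomial cohorts are pooled.
- **Entry PCT:** define it as the first sample at admission or suspicion, not a later value, and say how a missing value is handled.
- **Crude tests:** keep them as sensitivity analyses.

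With equal allocation, Mantel-Haenszel weights are close to proportional to stratum size, so the risk difference still addresses essentially the same overall contrast as the crude one. The method also avoids the separation problem of a logistic model.

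The cost is a change of wording, with no new patients, measurements or clinical procedures. The article describes recruitment and follow-up as running to December 2019, so the change should be fixed and dated before outcomes are compared by arm. If that comparison has already been made, the stratified results should be labelled as added afterwards.

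### Logistic-model variables are chosen by univariate p-value with an open threshold; the arm is not forced in, post-randomisation variables are not kept out, and chosen factors are judged at p<0.05

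*Protocol article*

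**What the plan says.** The Statistical analysis section of the protocol article plans a "multivariate logistic regression analysis will be performed on those variables with statistical significance or a clear tendency in the univariate analysis". The aim is "to detect which factors represent a protective factor or not, in terms of quality". The same section sets p<0.05 as significant. It gives no cut-off for a tendency and no list of candidates, and it names no variable as always included or always excluded.

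Two other sections give the model its meaning. Under Outcomes, the ultrasound and procalcitonin protocol "will be considered an improvement in the quality of care if a reduction in the prescription of antibiotics is observed", together with fewer days on antibiotics. Under Methodology, the arm decides which image comes first and the image then drives the advice: "If LUS is suggestive of bacterial pneumonia, regardless of PCT value, an antibiotic will be recommended". The control arm has the matching rule for chest X-ray.

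Separately, categorical variables are compared by chi-square and quantitative ones by t or Mann-Whitney tests. The Sample size section rests on an unadjusted comparison, "using a bilateral X^2^ test for two independent samples".

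**The concern.** The data that decide which variables enter the model also supply the p-values by which those variables are declared protective. The final p-values take no account of that selection. Because the threshold is open, it can be settled after the univariate results are known.

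Two further consequences are conditional on what the investigators treat as a candidate:

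- **The arm.** Quality is defined by antibiotic use under the new protocol, so the arm is a natural candidate factor. The rule would keep it only when its univariate result is already favourable to inclusion. Adjusted arm effects would then come from a filtered set of results.
- **The image result.** It arises after randomisation, depends on the arm, and leads to the antibiotic advice. It is therefore closely tied to prescription by design. If offered to the screen it is likely to pass, and adjusting for it blocks the path by which the arm acts.

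At stake are the adjusted and protective-factor results, which could be reported as confirmed findings when they are partly products of selection, multiplicity or adjustment for a mediator.

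**Working it through.** **Inputs from the protocol article.** Two-sided alpha 0.05; 80% power; "63 units in the control group and 63 units in the experimental group" for community pneumonia (126) and 28 per group for nosocomial pneumonia (56), so 182 in all.

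**Inputs assumed, because the article gives none.** Entry cut-off (0.10 unless stated), number of candidates (5 to 15), antibiotic rates, arm effects, image rates, and pooling of the two pneumonia types where n=182 is used.

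**The plan's own figure.** No figure is attached to the model. The 63 and 28 per group cannot be reproduced, because p1 and p2 appear only as symbols. The 63 is compatible with, for example, 0.80 against 0.57 (uncorrected formula: 62.8, rounded up). Nothing below depends on this.

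**Step 1: overstatement of the arm effect if it is screened.** For an estimate with mean μ on the z scale, kept only when Z>c:

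E[Z | Z>c] / μ = 1 + φ(c−μ) / {μ[1−Φ(c−μ)]}, with μ = 1.96 + z(power).

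| Entry cut-off | Power | μ | c−μ | φ / (1−Φ) | Factor |
|---|---|---|---|---|---|
| 0.05 (c=1.96) | 50% | 1.960 | 0 | 0.3989/0.5000 = 0.798 | 1.41 |
| 0.05 | 80% | 2.802 | −0.842 | 0.2800/0.8000 = 0.350 | 1.12 |
| 0.10 (c=1.645) | 50% | 1.960 | −0.315 | 0.3796/0.6237 = 0.609 | 1.31 |
| 0.10 | 80% | 2.802 | −1.157 | 0.2043/0.8763 = 0.233 | 1.08 |

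The plan also admits a tendency, so the 0.10 rows fit its wording better than the 0.05 rows. The factors apply to the log odds ratio.

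A simulation agrees (n=126, arm plus 10 null covariates, 70% antibiotic use in controls, 2,000 runs per setting, entry at 0.10):

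- True odds ratio 0.60: the arm was left out of 62% of models. When it entered, the odds ratio averaged 0.41, a log-scale factor of 0.889/0.511 = 1.74 (power here was only 28%).
- True odds ratio 0.45: left out of 32%, averaging 0.37 when in, a factor of 1.006/0.799 = 1.26 (power 58%).
- Arm always in the model, alone: 0.59–0.60 and 0.44–0.45, essentially unbiased.

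**Step 2: adjusting for the image result.** Assume a suggestive image in 45% (ultrasound) and 70% (X-ray), and antibiotics in 95% if suggestive and 35% if not, whatever the arm.

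- Ultrasound arm: 0.45×0.95 + 0.55×0.35 = 0.62.
- X-ray arm: 0.70×0.95 + 0.30×0.35 = 0.77.
- Unadjusted odds ratio: (0.62/0.38)/(0.77/0.23) = 0.49.
- Odds ratio given the image result: 1 by construction.

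Simulated trials gave 0.47–0.49 unadjusted and 1.01 adjusted. The loss is complete because the assumption sends the whole arm effect through the image; with partial mediation the loss would be partial.

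**Step 3: chance factors.** For k independent null candidates tested at 0.05, P(at least one) = 1 − 0.95^k. Simulation: n=182, outcome rate 0.6, binary null covariates, 3,000 runs.

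| k | 1 − 0.95^k | With 0.10 screen | No screen, all in one model |
|---|---|---|---|
| 5 | 23% | 22% | 23% |
| 10 | 40% | 40% | 43% |
| 15 | 54% | 53% | 61% |

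A further run gave 20/40/54% with the screen and 21/43/59% without. The screen does not raise this rate. What it does change is how the final p-values read: in the n=126 simulation with no arm effect, null covariates that had passed a 0.10 screen were significant 46% of the time, against a nominal 5%.

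**The case against.** The strongest reply is that this is a secondary factor search and not the estimator of the treatment effect. The sentence does not name the arm, no section promises an adjusted arm effect, and no section lists the image result as a candidate. The article is condensed, so a candidate list may stand in the full protocol or analysis plan. The primary comparisons are unadjusted and pass through no screen.

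Most of this stands, and it limits the point. A reader might infer that the plan withholds the treatment effect unless it is significant, or that it intends to adjust for the image. The article supports neither: the arm's candidacy is inferred from the quality aim and the lack of any exemption, and mediator adjustment is only permitted by the rule. A reader might also blame the screen for the 20–55% rate of chance factors. Step 3 shows that rate with or without the screen.

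What does not stand is treating the matter as an omission. The entry rule is stated, its threshold is open, and its results are to be judged at p<0.05 without an exploratory label.

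**Conclusion.** The concern holds in a limited, partly conditional form. Unconditionally, selection is by same-data p-value with an undefined threshold, and factors are declared at 0.05 with no allowance for selection or for the number tried. Conditionally on the arm being a candidate, its reported adjusted effect is overstated by about 1.3 times at 50% power or 1.08 times at 80%, with an assumed 0.10 cut-off. Conditionally on the image result entering, the arm effect can shrink, and it disappears if the image carries all of it.

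The direction of the selection bias does not depend on the assumed inputs, but all the sizes do. The randomised chi-square, t and Mann-Whitney comparisons are untouched. This is worth correcting, but it does not threaten the main unadjusted result.

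**What to change.** Replace the univariate screen with one pre-specified logistic model for antibiotic prescription. Always include arm, with a short list of baseline covariates chosen on clinical grounds, for example pneumonia type, baseline procalcitonin and age. Exclude image results and all other post-randomisation variables. Label any further search for factors exploratory and attach no significance claims to it. That label and the short list are what deal with multiplicity; deleting the screen alone would not.

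The cost is a change of analysis wording, with no extra patients or visits. Pneumonia type, procalcitonin and age already figure in the sample size, the algorithm and the eligibility criteria. The article does not list the recorded data items, so the sponsor should confirm that each covariate is recorded as a baseline value. The downside is that the factor search loses its confirmatory wording.
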